## **2. Data analysis plan – Data description**

### **2.1 Baseline comparability of randomised groups**

Baseline descriptions of participants by treatment and overall will be reported using means and standard deviation or numbers and proportions as appropriate. No significance testing will be used.

### **2.2 Loss to follow-up and other missing data**

The number of the participants withdrawing from the trial and the reasons why will be summarised.

### **2.3 Adverse event reporting**

Adverse events and serious adverse events will be summarised by treatment arm.

### **2.4 Assessment of outcome measures (unblinding)**

Evidence for unblinding of treatment to interviewers will be studied.

### **2.5 Descriptive statistics for outcome measures**

#### Primary endpoints

The primary endpoint of the RCT is to evaluate the benefit of intensive blood pressure control on the normalization/ limitation of cardiovascular target organ damage as assessed by LV mass index. The principal outcome measure will be the change in LV mass index from baseline in each treatment arm for each year of follow-up.

#### Secondary endpoints

RWT will be a secondary endpoint. Change in RWT in each treatment arm will be secondary outcome measures and will be reported as described for the primary outcome.

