| Trial Design                                     | Interventional multi-centre RCT UK-wide national trial                                                                                                                                                                                                                                                                                                                                                                                                                                                                                                                                                                                                                                                             |
| Endpoints                                        | 1. The primary endpoint of the RCT is to evaluate the benefit of aggressive blood pressure control on the normalization/ limitation of cardiovascular target organ damage as assessed by LV mass. The principal outcome                                                                                                                                                                                                                                                                                                                                                                                                                                                                                            |

|                                         |                                                                                                                                                                                                                                                        |
|-----------------------------------------|--------------------------------------------------------------------------------------------------------------------------------------------------------------------------------------------------------------------------------------------------------|
|                                         | measure will be the differences in LV mass between aggressive and standard treatment groups.
2. cIMT and PWV are secondary endpoints. Differences in cIMT and PWV will be secondary outcome measures.                                               |

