#### **Primary objectives**

1. a) Examine the relationship of LVM, IMT and arterial stiffness to blood pressure (following adjustment for confounders) in a cohort of children with and without CKD.  
b) Compare these measures in children with and without CKD when adjusted for peripheral and central blood pressure.
2. Perform a randomised controlled trial to determine whether aggressive blood pressure reduction (below the 40th percentile) compared to standard care (below the 75th percentile) is effective in normalising left ventricular mass, arterial structure/function.

**Secondary objectives** will be to examine the effects of aggressive versus standard blood pressure reduction on microalbuminuria and progression of renal failure and to determine if biomarkers of arterial injury/ventricular load are independently related to cardiovascular target organ damage.

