### **2.2 Trial Design & Flowchart (Appendix 2)**

*A description of the design of trial to be conducted (eg double-blind, single-blind, open label, placebo-controlled, parallel-group, double-dummy, cross-over, etc.) should be given. Please also include a schematic diagram (flow chart) of trial procedures and stages is desirable as it is particularly useful for determining activities involved during each clinic visit (eg blood tests or scans, treatment, diary completion, adverse event monitoring, physical examination etc).*

The principal outcome measure for the controlled trial will be the differences in LV mass between aggressive and standard treatment groups.

Differences in IMT and PWV will be secondary outcome measures.

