**Statistical Analysis Plan**

## A) QUANTITATIVE ANALYSIS PLAN

### 1. Description of the trial

#### 1.1 *Principal research objectives to be addressed*

This study will determine whether controlling blood pressure to a lower level than is currently recommended will prevent the damage to arteries and heart.

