##### Secondary objectives

Secondary objectives will be to examine the effects of aggressive versus standard blood pressure reduction on relative wall thickness and progression of renal failure.

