**Table 1. Trial Completion dates**

| Key task completion date (months)            | Day 1                                 | 4-mths | 8-mth | 1 year | 2 year | 3 year |
|----------------------------------------------|---------------------------------------|--------|-------|--------|--------|--------|
| Patient information and informed consent     | Over first 12 months of study         |        |       |        |        |        |
| Physical examination                         | At recruitment and at least 4 monthly |        |       |        |        |        |
| Demographics                                 | √                                     | √      | √     | √      | √      | √      |
| Clinic BP and review of medications          | √                                     |        |       | √      | √      | √      |
| ABPM (in sub-group)                          | √                                     |        |       | √      | √      | √      |
| Central BP evaluation                        | √                                     |        |       | √      | √      | √      |
| Blood sample                                 | √                                     |        |       | √      | √      | √      |
| Urine sample                                 | √                                     |        |       | √      | √      | √      |
| Non-invasive arterial studies (cIMT and PWV) | √                                     |        |       | √      | √      | √      |
| Echocardiography                             | √                                     |        |       | √      | √      | √      |
| 24-hour ambulatory BP monitoring             | √                                     |        |       | √      | √      | √      |

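### The SAP's only secondary endpoint is relative wall thickness, in conflict with the protocol's cIMT and PWV, and its renal objective is tied to no outcome variable

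*Combined protocol and SAP*

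**What the plan says.** **Protocol.** The endpoints row of the Study Synopsis reads: "cIMT and PWV are secondary endpoints. Differences in cIMT and PWV will be secondary outcome measures". Section 2.2 repeats it: "Differences in IMT and PWV will be secondary outcome measures". Section 2.4.1 gives a within-subject SD for PWV of 0.5 m/s and a detectable difference in change of 0.3 m/s. The randomised-trial objective covers arterial structure and function as well as LV mass. The secondary objectives (section 2.1) are to study effects "on microalbuminuria and progression of renal failure and to determine if biomarkers of arterial injury/ventricular load are independently related to cardiovascular target organ damage". Relative wall thickness (RWT) appears in the echocardiography methods, with a cut-off of 0.41, to classify ventricular geometry. It is not listed as an endpoint.

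**SAP.** Section 1.1 keeps the question whether lower blood pressure "will prevent the damage to arteries and heart", but its primary objective names LV mass only. Its secondary objectives concern effects "on relative wall thickness and progression of renal failure". Section 2.5 gives one secondary endpoint: "RWT will be a secondary endpoint", to be reported in the same way as the primary outcome. Table 1 keeps the cIMT and PWV row at day 1 and years 1, 2 and 3. Section 1.7 collects creatinine, cystatin C and the mean of three urinary albumin:creatinine values, and assigns none of them to an outcome.

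**The concern.** An analyst who follows SAP sections 2 and 3 literally would analyse LV mass index and RWT and then stop. The two secondary endpoints that the protocol named, one of them with its own detectable difference, would go unreported. So would the arterial half of the question that SAP 1.1 still asks. For the kidney the problem is different. The objective survives, but eGFR slope, a percentage fall in eGFR, reaching kidney failure, or change in albuminuria would all satisfy it, and the SAP excludes none of them. In an open-label trial, secondary outcomes should be fixed in writing so that the choice cannot follow the data.

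**Working it through.** **1. Endpoints and objectives side by side.**

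| Item | Protocol v1.2 | SAP |
|---|---|---|
| cIMT | Secondary endpoint (Synopsis, 2.2) | Scheduled in Table 1; no endpoint |
| PWV | Secondary endpoint, with detectable difference (2.4.1) | Scheduled in Table 1; no endpoint |
| RWT | Geometry measure (echocardiography methods) | Only secondary endpoint (2.5) |
| Renal progression | Secondary objective; no variable defined | Secondary objective (1.1); no variable defined |
| Microalbuminuria | Secondary objective | Absent as an objective; urinary albumin:creatinine collected (1.7) |
| Biomarkers | Secondary objective | Absent as an objective; samples collected (1.7) |

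Count: 2 of 2 named protocol secondary endpoints are not SAP endpoints. 1 of 2 SAP secondary objectives has no variable.

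**2. Is the SAP consistent with itself?** Some arterial content remains: the question in 1.1, the cIMT and PWV row of Table 1, and the exclusion in 1.3 of children who cannot undergo study measurements, with PWV as an example. Other arterial content has gone. The primary objective no longer mentions arteries. Section 1.7 omits the protocol's cIMT and stiffness methods. Section 1.2 blinds the clinical team to echocardiogram findings only, where the protocol also covered the vascular studies. The SAP as it stands neither keeps the arterial endpoints nor says that they were removed.

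**3. The protocol's PWV figure.** Inputs from protocol 2.4.1: SD 0.5 m/s, 60 per arm, and a difference of 0.3 m/s. The 90% power and P<0.05 are stated there for LV mass index and are assumed to carry over. The test is assumed two-sided.

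- Detectable difference = (1.960 + 1.282) × SD × √(2/n) = 3.242 × 0.5 × √(2/60) = 0.296 m/s. This reproduces the stated 0.3.
- Required n per arm = 2 × (3.242 × 0.5 / 0.3)² = 58.4, so 59.
- Power at 0.3 with 60 per arm: 0.3 / (0.5 × √(2/60)) − 1.960 = 1.326, which gives 90.8%.

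This takes 0.5 as the SD of the change. If 0.5 is instead the SD of a single reading within a child, the SD of the change is 0.5 × √2 = 0.707. The detectable difference is then 3.242 × 0.707 × √(2/60) = 0.418 m/s, and power at 0.3 is about 64%. Under the first reading PWV was an endpoint that the protocol's sample size could serve. Under the second it is weaker, but still a named endpoint.

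**4. Is there a model that could be applied?** Yes. Protocol 2.4 and SAP 1.9 describe a mixed model for outcomes in general, and SAP 3.1 describes yearly slopes and their difference between arms without restricting them to LV mass index. None of these sections names an arterial or renal variable. What the SAP lacks is the list of outcomes to which the model applies.

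**The case against.** The best defence is that the SAP made a deliberate reduction in scope and left some text behind. The edits in step 2 point that way. The sentence on arteries and the Table 1 row both repeat protocol text, so they are weak evidence of continuing intent. This stands as a plausible explanation, and for that reason the fix includes a route for endpoints that were really dropped. It does not remove the conflict, because the available SAP text gives neither a statement of the change nor a reason.

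Four further points on the other side:

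- A reader might infer concealed outcome switching. The documents do not support that. Some pages were removed from the public text, including material directly before the SAP, and a version history or a reason could lie there. All that can be said is that no reason appears in what is available.
- A reader might infer that no analysis of these outcomes was planned at all. That is too strong, as step 4 shows.
- The protocol defines no renal endpoint either, and its section 4.1.2 on secondary efficacy parameters is marked not applicable. Both are true. The SAP inherited the renal gap, but it is the document that should close it. The entry in 4.1.2 does not cancel the Synopsis and section 2.2.
- RWT is not a new measurement; only its status as an endpoint is new. This is correct.

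**Conclusion.** The concern holds as a conflict between the protocol and the SAP. Both of the protocol's named secondary endpoints are missing from the SAP's endpoints, RWT takes their place, and the SAP's renal objective has no outcome variable. This is more than missing detail, because the SAP followed as written leaves the named secondary endpoints unanalysed although their measurements are scheduled four times. The primary analysis of LV mass index is not affected.

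The conclusion rests on the text available and makes no claim about motive. That the SAP is later than protocol v1.2 is an inference: SAP 1.5 describes randomisation in the past tense, and SAP 1.2 gives a sample size of 144 against the protocol's 150. The PWV arithmetic also assumes that the 90% power and two-sided 5% level apply to PWV. The conflict itself depends on neither assumption.

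**What to change.** In SAP 2.5 and 3.1:

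- Restore cIMT and PWV as secondary endpoints, with the same mixed model as LV mass index, and carry their measurement methods into SAP 1.7.
- Have the sponsor name the PWV method. The protocol plans arm-thigh PWV in every child and carotid-femoral PWV in those able to co-operate. It concedes that the arm-thigh method is not a recognised standard and reports a correlation of 0.7 between the two. It does not say which is the endpoint. Both can be reported.
- Tie the renal objective to a variable already collected, such as annual change in eGFR. Add albumin:creatinine ratio for the protocol's microalbuminuria objective, or state that this objective was withdrawn.
- Label RWT as an endpoint added after protocol v1.2.

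If the arterial endpoints were deliberately dropped, state the date and reason instead, and align SAP 1.1 and Table 1. The renal variable is still needed in that case.

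The cost is a few lines of SAP text and some further runs of an existing model. There would be a few more secondary comparisons, to be reported as such. The benefit also depends on how complete the arterial data are. The supplementary results available show LV, blood pressure and medication data but no cIMT or PWV, so completeness cannot be judged from these documents.

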## **3. Data analysis plan – Inferential analysis**

Analysis will be completed according to an intention to treat principle.

### **3.1 Main analysis of treatment differences**

Mixed effects models will be used to estimate the mean annual rate of change and the difference in these rates between treatment arms. Models will account for baseline and all subsequent follow-up time points.

#### **3.1.1 Model assumptions**

Mixed effect models will assume a linear change in outcome over time.

It will be assumed that there is no difference between treatment arms at baseline (as confirmed by baseline comparability (Section 2.1).

Missing data from loss to follow-up/withdrawal will be assumed missing at random.

### **3.1.4 Sensitivity analyses**

Sensitivity analyses relaxing the assumptions of a linear change in outcome over time will be completed.

### **3.2 Interim analysis**

Interim analysis to be performed at 1-year by the statistical team to check if the SD of measured indexed LV mass (LVMI) is in keeping with initial projections. The choice of standard deviation (SD) for the initial sample size was made using the best data available at the time of the study design. In accordance with good practice, we will monitor the SD during the study across the whole study group i.e. NOT by randomised group. In this way we can verify that the overall SD observed in the trial is in fact as expected. If the SD is found to be very different, either larger or smaller, we will consider whether the sample size calculations need to be revised accordingly. In this way we will be able to be as certain as is possible that the trial is powered as planned and ensure that the primary study endpoint is achieved. We will inform the Research Ethics Committee of the results of the interim analysis soon after the end of the 1st year.

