## EXPERIMENTAL DESIGN AND METHODS

### Protocol

**Subjects** (n=150, to give n=120 complete) will be aged 2 to 15 years with CKD stages 1-4 in the last 12 months. Subjects will be eligible to enter the study whilst on anti-hypertensive/s medications irrespective of recent change/s in anti-hypertensive therapy. Detailed inclusion and exclusion criteria are described later in this document under 'Section 3'. Subjects with arterio-venous fistulae, on dialysis or those with a previous kidney transplant at the time of study entry will be excluded. eGFR will be

calculated using the Schwartz formula and CKD staged as per existing definitions [31,32]. Patients who reach end stage renal failure and commence dialysis or receive a kidney transplant will stop participating in the 'randomised controlled trial' but continue to have measurements performed until the end of the study. Informed consent/assent will be obtained from parents and patients (if age applicable) for participation in the study, as per institutional ethics committee approval. A control group (n=120) of age matched children without CKD will be included with all proposed study related investigations to be performed at baseline and at annual intervals. These will be recruited from siblings of study subjects and from a local community using links from a school based liaison project. In addition we aim to recruit a further control group (n=30) of subjects with systolic BP <50th percentile but on no anti-hypertensive medication.

All study related investigations at 'baseline' will be performed just before randomisation. Following enrolment and performance of baseline investigations children with CKD will be randomised to the two arms of the study: aggressive BP control (below the 40th percentile) or standard BP control (between 50th-75th percentile). A minimisation procedure will be used to ensure that patients randomised to the two arms are matched for: age, gender, CKD stage and proteinuria. Children will be recruited over the first 12-months of the study and will therefore have at least 2-years of follow up. Following randomisation all children in whom blood pressure is not to target will be reviewed at 2-4 weekly intervals. Thereafter all children will be monitored at least 4-monthly at the time of routine hospital visits and have clinic BP maintained in the assigned target range over the duration of the study.

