### 2.4.1 Sample Size

The outcome data are longitudinal and so we will fit a model that takes account of this data structure. The random effects model is a 2-level multilevel model that allows for the repeated data within subjects, while allowing some measurements to be missing. (This is preferred to repeated measures analysis of variance that requires complete data on all subjects). For a particular outcome, eg LVmass, the baseline value for each subject will be included in the model to adjust for (random) baseline variability between subjects. The results of the analysis are in the form of mean difference in LVmass between the intervention and control groups, at the endpoint, with a 95% CI.

The original sample size calculations were based upon longitudinal measurements of LVMI at annual intervals in our cohort of children with CKD (n=47). The SD of change in LVMI is 7.7 g/m2.7 and this was obtained without the same standardized reading of LVM that we are proposed in the study. To be conservative we assume just a 20% improvement on our existing data giving an SD of 6 g/m2.7 result from our own cohort. Thus with n=60 in each group we should be able to

detect a difference in change in LVMI of  $> 3.1 \text{ g/m}^{2.7}$  (=9% of baseline LVMI) over the 2 year duration with 90% power ( $P<0.05$ ). This is one third of the difference ( $9.4 \text{ g/m}^{2.7}$ ) between subjects in our cohort that have blood pressure in the 50-75th and below 40th percentiles. Although we are assuming relatively rapid tracking of LV mass in relation to blood pressure, this is not unreasonable given the time frame of LV regression in adults. A recent meta-analysis [Fagard et al, *Hypertension* 2009; 54:1084] of randomized studies shows a mean change in LVMI of 10.3% over duration of 6 months.

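### The 1-year check is worded for the SD of measured LVMI and timed before change scores exist, so it cannot verify the SD of change on which the sample size rests

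*Combined protocol and SAP*

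**What the plan says.** **What is monitored.** SAP 3.2 and protocol 2.4.1 define an interim look at 1 year "to check if the SD of measured indexed LV mass (LVMI) is in keeping with initial projections". Protocol section 9 (Analysis) repeats this in nearly the same words. The SD is to be taken over the whole study group and not by arm. If it proves very different from expectation, in either direction, the team will consider revising the sample size.

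**What it is meant to verify.** SAP 3.2 links the look to the planning assumption: "The choice of standard deviation (SD) for the initial sample size was made using the best data available at the time of the study design". The stated aim is to be confident that the trial is powered as planned.

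**What the sample size rests on.** Protocol 2.4.1 and SAP 1.8 start from earlier longitudinal data: "The SD of change in LVMI is 7.7" g/m^2.7 (n = 47, annual intervals). Then "we assume just a 20% improvement on our existing data giving an SD of 6 g/m"^2.7. With 60 per group, the trial is said to be able to "detect a difference in change in LVMI of" more than 3.1 g/m^2.7 over 2 years with 90% power.

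**When the look happens.** Protocol 2.4.3 and section 9 place it 1 year after the study starts. The Protocol subsection of Experimental Design and Methods says: "Children will be recruited over the first 12-months of the study and will therefore have at least 2-years of follow up". Protocol 2.3 and SAP Table 1 schedule echocardiography at day 1 and then annually.

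**The concern.** The SD of a measurement across children and the SD of change within children are different quantities. The first reflects how much children differ from one another. The second reflects how much a child's value moves, plus measurement error. They are linked only through the correlation between a child's two measurements, and the look does not estimate that correlation. The documents give neither a value for it nor a projected SD of measured LVMI for the sample size, so the look has no like-for-like benchmark.

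Timing adds a second problem. When recruitment has only just finished, nearly all available echoes are baseline echoes. The SD that could be computed is essentially a baseline SD, whatever the wording intends.

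What is at stake is the planning SD of 6. It is lower than the only SD of change the sponsor had observed (7.7), on the expectation that standardised reading would reduce it. This look is the one step in the plan said to test that expectation.

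**Working it through.** **Inputs**
- Planning SD of change 6; observed SD of change 7.7; 60 per arm; difference 3.1; P < 0.05 (protocol 2.4.1, SAP 1.8). Sidedness is not stated. Results are to be given with a 95% CI, so two-sided is taken.
- SD of measured LVMI 9.1 (n = 49), from the sponsor's earlier cohort (protocol section 1).
- SD of measured LVMI at trial baseline 10.1 (n = 64) and 8.1 (n = 60), from supplementary Table S2. Pooled: sqrt[(63 x 10.1^2 + 59 x 8.1^2)/122] = 9.19. These are later data, used only to show that 9.1 is realistic.

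**Step 1. The plan's own figure.** Power = Phi[3.1/(SD x sqrt(2/60)) - 1.96]. With SD 6 this is Phi(2.83 - 1.96) = 0.808. The stated 90% is not reproduced. On these inputs 60 per arm gives about 81% two-sided (88% one-sided), and 90% two-sided would need 79 per arm. This is a separate issue, but 81% is the base used below.

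**Step 2. Level SD set against 6.** 9.1/6 = 1.52, so the SD would look about 50% too large. Required n scales with SD^2: 60 x (9.1/6)^2 = 138 per arm, at the unchanged power of about 81%.

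**Step 3. What a level SD of 9.1 says about change.** Assume equal variance at both visits. Then SD_change = SD_level x sqrt[2(1 - r)], so r = 1 - SD_change^2/(2 x SD_level^2).
- SD of change 6: r = 1 - 36/165.62 = 0.78.
- SD of change 7.7: r = 1 - 59.29/165.62 = 0.64.

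The same 9.1 is therefore compatible with the planning value being right and with it being too low.

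**Step 4. Power at 60 per arm over a range of r.** Unadjusted power uses SD_change. Baseline-adjusted power uses residual SD = 9.1 x sqrt(1 - r^2), because protocol 2.4.1 and SAP 1.9 plan to adjust for baseline.

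| r (assumed) | SD of change | Power, unadjusted | Residual SD | Power, adjusted |
|---|---|---|---|---|
| 0.50 | 9.10 | 46% | 7.88 | 58% |
| 0.64 | 7.7 | 60% | 6.98 | 68% |
| 0.70 | 7.05 | 67% | 6.50 | 74% |
| 0.78 | 6.0 | 81% | 5.66 | 85% |
| 0.90 | 4.07 | 99% | 3.97 | 99% |

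The rows for 0.64 and 0.78 use the unrounded correlations 0.642 and 0.783. With the level SD held at 9.1, power runs from 46% to 99% unadjusted and from 58% to 99% adjusted. The level SD does not determine power under either analysis.

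**Step 5. Would change scores exist?** A child has a year-1 change score at the look only if recruited at or near the first day of the study. Recruitment is planned across the whole 12 months, so almost none would.

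**Step 6. Does pooling over arms spoil the remedy?** If the true SD of change is 6 and the full 3.1 difference is present, the pooled SD is sqrt(36 + 3.1^2/4) = 6.20. The inflation is small, so the check can stay blinded.

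**The case against.** The strongest reply is that the wording is loose and the intent sound. SAP 3.2 ties the monitored SD to the one chosen for the initial sample size, and the only SD chosen for that purpose is the SD of change. That reading is fair and may be what was meant. However, the text does not say that change will be computed, and the measured-LVMI wording appears in three places. The timing problem also remains on that reading.

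A second reply is that this is not the only look at the data. SAP 3.2 also speaks of monitoring the SD during the study, and the data monitoring committee reviews all collected data annually. Both could allow a later check, but neither names the SD of change.

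A reader might infer that the check would force a wrong resizing, for example to 138 per arm, or would falsely pass the trial because the SD matched 9.1. The documents support neither. Revision is only to be considered, with no numerical threshold. The 9.1 is background description of an earlier cohort and is nowhere set as a benchmark. Nor is there ground to infer a biased treatment effect: the look is pooled over arms and concerns power.

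It also stands that unadjusted figures overstate the loss. With the planned baseline adjustment, the contrast is 85% against 68%, narrower than 81% against 60%.

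**Conclusion.** The point holds in a limited form. As worded, the 1-year check compares unlike quantities; as timed, it would have almost no change scores to work with. It therefore cannot verify the planning SD of 6. The consequence is a safeguard on power that gives no information, under a discretionary rule.

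The size is illustrative. If the SD of change is 7.7 and not 6, power for a 3.1 difference at 60 per arm falls from about 81% to 60% unadjusted. On the level SD of 9.1, the baseline-adjusted fall is from about 85% to 68%. A level SD of 9.1 could not tell these cases apart. The figures rest on a two-sided 5% test, the normal approximation, equal variance at both visits, and a correlation that the documents do not give.

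**What to change.** In SAP 3.2, protocol 2.4.1 and protocol section 9:

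1. Replace the SD of measured LVMI with the SD of change in LVMI from baseline, pooled over arms, and compare it with 6. State the interval, for example baseline to year 1; the 7.7 also came from measurements at annual intervals.
2. Do the check once a pre-stated number of children have a year-1 echo (60, for example), not at 1 calendar year.
3. If a residual SD given baseline, or the SD of slopes from the planned mixed model, is preferred, derive a benchmark for that quantity. Do not compare it with 6: in the illustration the residual SD is about 5.7 when the SD of change is exactly 6, so the comparison would lean towards reassurance.
4. If the check has already been done, state which SD was computed and on how many children.

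The cost is a paragraph of text, and the check happens some months later. Blinding is unaffected.
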